## Abstract

**Background:**

Accidental falls by older patients in hospital are one of the most commonly reported adverse events. Falls after discharge are also common. These falls have enormous physical, psychological and social consequences for older patients, including serious physical injury and reduced quality of life, and are also a source of substantial cost to health systems worldwide. There have been a limited number of randomised controlled trials, mainly using multifactorial interventions, aiming to prevent older people falling whilst inpatients. Trials to date have produced conflicting results and recent meta-analyses highlight that there is still insufficient evidence to clearly identify which interventions may reduce the rate of falls, and falls related injuries, in this population.

**Methods and design:**

A prospective randomised controlled trial (n = 1206) is being conducted at two hospitals in Australia. Patients are eligible to be included in the trial if they are over 60 years of age and they, or their family or guardian, give written consent. Participants are randomised into three groups. The control group continues to receive usual care. Both intervention groups receive a specifically designed patient education intervention on minimising falls in addition to usual care. The education is delivered by Digital Video Disc (DVD) and written workbook and aims to promote falls prevention activities by participants. One of the intervention groups also receives follow up education training visits by a health professional. Blinded assessors conduct baseline and discharge assessments and follow up participants for 6 months after discharge. The primary outcome measure is falls by participants in hospital. Secondary outcome measures include falls at home after discharge, knowledge of falls prevention strategies and motivation to engage in falls prevention activities after discharge. All analyses will be based on intention to treat principle.

**Discussion:**

This trial will examine the effect of a single intervention (specifically designed patient education) on rates of falls in older patients in hospital and after discharge. The results will provide robust recommendations for clinicians and researchers about the role of patient education in this population. The study has the potential to identify a new intervention that may reduce rates of falls in older hospital patients and could be readily duplicated and applied in a wide range of clinical settings.

**Trial Registration:**

ACTRN12608000015347

## Background

Accidental falls are one of the most frequent adverse events reported in hospitals[1] with falls rates ranging from 2.2 falls per 1000 patient days on general acute medical wards[2,3] and up to 20 falls per 1,000 patient days on rehabilitation wards being reported.[4,5] Up to 30% of hospital falls result in injury[6] and fractures sustained from falls in hospitals have recently been found to result in poorer outcomes than fractures sustained from falls in the community.[7] In addition, falls are associated with poorer rehabilitation outcomes, increased length of stay (LOS) in hospital, increased costs, litigation, and increased risk of institutionalization.[1,8,9] Falls in the immediate period after discharge are also common for older people, further delaying recovery from hospitalisation,[10,11] with frequent injury and high levels of health care resource use also recorded.[12]

Recent meta-analyses have identified that there is only limited, if any, evidence for reduction of falls amongst hospital patients.[13,14] The small numbers of multifactorial randomised controlled trials (RCTs) conducted to date have included some large well designed studies that have demonstrated conflicting results. [15-18] These studies have used a variety of multifactorial interventions including, but not limited to, risk factor assessment followed by interventions targeted at each identified risk factor, patient exercise, education and environmental modification resulting in difficulty identifying the effective components. There is yet to be a large trial to determine the effect of a single intervention in this setting.

Falls prevention for older people following hospitalisation has been assessed in a limited number of randomised trials with equivocal results. [19-23] Patients followed up after discharge by an occupational therapist, who provided home environment modifications and training, showed a reduction in rates of falls,[20,21] but in contrast, a similar randomised trial only showed an effect in a subgroup of recurrent fallers.[23] In-hospital preparation is a feasible intervention for reducing falls in older patients after discharge. However a multifactorial programme, including systematic assessment and treatment of falls risk factors,[19] and a comprehensive geriatric assessment with follow up treatment[22] failed to reduce post discharge rates of falls.

Patient behaviour is an integral contributing factor to many in-hospital falls.[24,25] Thus strategies to modify patient behaviour may be an effective means to reduce rates of falls. Patient education is frequently cited as one component of multifactorial interventions.[15,17,26] Subgroup analysis of a previous randomised trial of a multifactorial falls prevention programme suggested that patient education was the most effective component in reducing falls.[27] However there has rarely been description of the theoretical frameworks underpinning development of content, and approaches to the delivery of education in trials to date. Thus there are few insights into the mechanisms by which it is thought patient education programs may reduce the rate of falls. Presenting this information would allow more reliable differentiation between successful and unsuccessful elements of content, and approaches to the provision of education programmes.

This study is the first randomised controlled trial to evaluate the effect of individual patient education for the prevention of falls in the hospital setting and also to investigate its effect on falls after discharge. The study will examine the optimal provision of patient education in this setting. It will also examine a theoretical framework that explains preventative health behaviours in order to understand falls after discharge.

### Research Questions

#### Primary research question

1. Does providing individual patient education for older patients in addition to usual care affect the rate of falls while in hospital compared to providing usual care alone?

#### Secondary research questions

2. Does providing individual patient education for older patients in addition to usual care affect the rate of falls after discharge compared to providing usual care alone?

3. Does providing individual patient education in addition to usual care affect patient length of stay in hospital or change in health related quality of life during admission?

4. Does providing individual patient education for older patients in addition to usual care influence patients' pre – discharge self – perceived risk of falls, knowledge about falls and falls prevention, motivation to engage in self protective strategies in the first six months after discharge, or their levels of participation in falls prevention activities after discharge?

5. Does providing face-to-face health professional follow up in addition to multimedia patient education and usual care reduce falls compared to providing multimedia patient education and usual care?

## Methods and design

### Study Design

This study is a three group prospective randomised controlled trial (see Figure 1), with blinded weekly follow-up and discharge assessments of participants in the hospital setting. In a sub-trial, participants at one site are subsequently followed up at home monthly by blinded assessors over a 6 month period.

**Figure 1 F1:**
[figure not shown]
**Participant flow through the study**.

### Location and Setting

Patients are being recruited from the geriatric assessment and rehabilitation unit, orthopaedic unit and acute/respiratory medicine unit of Princess Alexandra Hospital (PAH), Brisbane, Queensland and the rehabilitation and stroke unit, and medical and surgical wards of Swan Districts Hospital (SDH), Perth, Western Australia.

PAH is a 700 bed tertiary facility in Queensland and SDH is a 194 bed general hospital, serving the eastern region of the Perth metropolitan area.

The acute wards at both hospitals admit older patients who are undergoing short stay surgical and medical treatment for a variety of cardiac, respiratory and orthopaedic conditions or other medical or surgical diagnoses. The sub acute rehabilitation wards and stroke units admit older patients who are undergoing acute care for stroke, or longer rehabilitation for a variety of geriatric conditions including cardio-respiratory conditions, fractures, falls, stroke, Parkinson's disease and other geriatric management.

### Population and Recruitment

Patients eligible for inclusion in the study are individuals who are admitted to a participating ward at PAH or SDH, are 60 years of age or older, are able to provide written consent (or, for patients with cognitive impairment, have a family member/carer who can provide written consent) and have not previously been enrolled in the study. Recruitment commenced in January 2008 and there are currently 1150 participants enrolled in the trial.

### Intervention/Control conditions

#### 1. Usual care

Usual care on the medical and surgical wards consists of 24 hour availability of nursing and medical care, daily physiotherapy, and referrals to other allied health professionals as required. On the restorative and stroke units there are also daily occupational therapy sessions, and social work assessment and management provided. Therapy on all wards is usually provided 5 days per week. Locally developed falls risk assessment tools (unpublished) are used at both sites and special arm bands are provided to patients assessed as being at high risk for falls.

**Figure 2 F2:**
[figure not shown]
**Health Belief Model adapted to falls prevention education**. The constructs of the HBM applied to the application of the education intervention.

Specifically, the content:

a) Informs participants of the risk of falls and fall-related harm to provide participants with accurate information regarding the risks they face,

b) Informs participants of falls prevention strategies that they could undertake within the hospital setting,

c) Fosters participant belief that they could successfully undertake falls prevention strategies and that if undertaken, their risk of falling will reduce,

d) Provides a cue for action by facilitating participant planning to undertake falls prevention strategies.

Information presented under aims a) and b) is based upon local data and data presented in previous research.[7,24,25]

The workbook follows the recommended principles of design for written patient education materials and can be used by people with low functional health literacy.[32,33] A 20 point font in Arial and 1.5 line spacing is used within an A4 format (24 pages in total). The workbook contains a mixture of text, colour graphics and photographic images printed on matt paper. The readability level of the workbook was assessed at 7^th ^grade level using the SMOG readability formula.[34]

In the DVD, words are spoken verbatim and the manner of speech follows recommended principles for clear oral communication.[33] The DVD is 14 minutes in duration and was edited using Pinnacle Studio Plus version 9 software. The DVD is played on a portable Digital Video Disk Player (Dick Smith Electronics, Australia, Model: DSE 9" G7137) that is loaned to the patient. Accompanying stereo headphones (Sony Australia, Model: MDRXD 100) minimise interference of ambient sounds from the hospital ward environment and transfer of information to other participants who may be in the control group. Headphones also assist delivery of the education to participants with sensory impairments.

Video presentation of information caters to patients with different learning styles (auditory, visual) and assists patients who have low functional health literacy, English as a second language or visual impairment to understand the content. The optimal way to retain information appears to be to hear it, see it, have it repeated and interact with it.[35,36]

##### • Health professional follow up visits

After the patient education is provided using the DVD and workbook, participants in group 3 receive follow up sessions conducted by a physiotherapist who has experience in hospital care for older patients and received training from the principal investigator prior to the study commencement. The physiotherapists have discretion over the duration of each participant session (usually between 15 and 35 minutes), and the total number of sessions provided (though the content of the program is intended to be covered in 4 sessions). Duration and number of training sessions may be influenced by personal, medical and environmental factors relevant to each participant. The progression of each session is based on the theoretical frameworks of the HBM specifically:

a) Perception of risk – which facilitates participants having an accurate perception of the risk of falls in hospital and appropriately identify their personal susceptibility to falls and fall-injury.

b) Knowledge of the risk and of the self protective strategies required to reduce the risk – which facilitates knowledge of the nature and mechanisms of falls and of current known falls prevention strategies.

c) Belief that using strategies will reduce risk – which facilitates the participant translating their knowledge into practical achievable short and longer term goals to prevent falls and promote safety in the hospital.

d) Facilitation of confidence and motivation to take action to reduce risk – which empowers and supports participants to act on their planned strategies.

### Outcome measures

The primary outcome measure is participant falls during both hospitalisation and the 6 month post discharge period. The definition of a fall used in this study is the World Health Organisation definition namely: "any event when the participant unexpectedly comes to rest on the ground, floor or another lower level."[37]

Secondary outcome measures being collected include length of stay in hospital, and change in health-related quality of life during hospitalisation, quantified using the EQ-5D instrument.[38] The EQ-5D is administered by face-to-face interview, with the question set presented to the participant in hard copy and read out by a research assistant.

Secondary outcome measures for participants in the home follow up sub-trial at the SDH site include a pre-discharge assessment using a survey (see additional file 1) of their self perceived risk of falls and falls injuries, knowledge about falls mechanisms, awareness of strategies to prevent falls at home and confidence and motivation to prevent falls at home after discharge. The survey items were developed by the investigative team during a previous randomised trial of the education materials.[28]

The final outcome survey (see additional file 2) administered to participants in the home follow up trial measures participants' engagement in falls prevention activities. The activities specified in the survey items were selected on the basis of current evidence for falls risk reduction when implemented amongst older community dwelling people.[39,40]

Demographic data being collected includes age, gender, falls in the 6 months prior to hospitalisation, admission and discharge residential living status, cognitive status using the Short Portable Mental Status Questionnaire,[41] mood using the Geriatric Depression Scale,[42] and medical diagnosis on admission.

### Procedure

Prior to commencement of recruitment, hospital staff working in participating wards were trained to apply the WHO definition of a fall, using 14 video-scenarios. This training was necessary as previous research indicates that absence of a definition is a barrier to documenting falls and that providing a written definition of a fall in itself does not considerably improve agreement between hospital staff as to what constitutes a fall.[43,44]

Baseline measurements are collected from participants after written consent has been obtained (or in the case of patients with cognitive impairment, where their carer or family has provided written consent). Participants are then randomised into one of the 3 groups. Participants in group 1 then continue to receive 'usual care'. Participants in group 2 receive the patient education via DVD and written workbook in addition to usual care. These participants have an opportunity to view the DVD within 24 hours of being allocated to this intervention. If the participant is too unwell to view the DVD immediately, they are provided with an opportunity to view the DVD as soon as practical after their health condition stabilizes. Participant family members, care-givers, or guardians are also invited to view the DVD and the workbook on regular workdays. Participants are asked if they wish to view the DVD again on a weekly basis until discharge and are encouraged to review their goals via interactive use of their workbook. The intervention is identical to that provided for participants in group 3 with the exception that there is no health professional follow-up visit. Participants in group 3 receive the patient education intervention described in group 2 and also receive the individual health professional follow-up visits. The health professional monitors these visits for time, content and participants' knowledge and achievement of their planned strategies.

This is a pragmatic trial and the interventions are provided in the usual hospital environment, most often at the bedside. Participants receive the intervention at a convenient time for optimal engagement. For example, if a participant becomes acutely unwell the investigator returns to complete the intervention when the participant is medically stable.

Research assistants, who are blinded to group allocation, check for falls occurrence on a weekly basis by reviewing medical records and interviewing staff and participants and their families. Periodic review of computerised hospital incident reporting systems is also undertaken.

At point of discharge, participants at the SDH site are administered the pre-discharge survey, given a falls diary and trained in how to record information in the diary. Participants and their families are subsequently followed up monthly by telephone for 6 months after discharge by research assistants to check for falls after discharge. Research assistants receive training from the investigator to question participants regarding falls occurrence and the circumstances of each fall reported. Participants in the home follow up trial are also administered the final outcome survey via telephone at 6 months post discharge from hospital. If participants have cognitive impairment, their carers assist them to respond to survey items. This procedure aims to maximise accuracy of the data collected about the participants' engagement in falls prevention activities.

A cross-sectional survey of hospital nursing, physiotherapy, occupational therapy, and medical staff will be conducted at the conclusion of subject recruitment to gauge level of staff awareness of participant group allocation. The survey will be conducted once only and hospital staff are informed of this so that they are not tempted to actively identify patient group allocation in order to respond more accurately in assessments they may anticipate taking place in future.

### Data Analysis

#### Primary Outcome

Data analysis will be performed on an intention-to-treat basis using a two-tailed alpha = 0.05. Falls rates in hospital will be analysed using Cox semi-parametric proportional hazards regression analysis (Anderson-Gill model for recurrent events) with the intervention groups entered as dummy variables. This allows multiple falls by individual participants, variations in patient length of stay, and time varying covariates to be incorporated into the analysis if required. Nelson-Aalen cumulative hazard plots will also be developed to graphically display cumulative fall rates over time for each of the groups. Visual analysis of these plots and the Schoenfeld residuals test will be used to check the proportional hazards assumption with this data. The proportion of participants having one or more falls in each group (being a faller) will be compared between groups using relative risk (95% confidence intervals).

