#### Sample size

Recent economic modelling of patient education for prevention of falls indicates this intervention may be a cost-effective approach for the prevention of falls with reductions in the proportion of people who fall in the order of 20% and possibly as low as 10%[12]. Previous in-hospital investigations have demonstrated reductions in falls per 1000 patient days in the order of 30% using targeted, multifactorial interventions, [17] and amongst specific patient subgroups as high as 49% using patient education alone[27]. Given this background context, and that the education is being provided to a reasonably unselected patient cohort, we anticipated that this intervention could reduce the rate of falls per 1000 patient days by 30%.

We conducted 1000 bootstrap simulations of data previously published from this setting [17] and determined that our experiment would have 80% power to detect a reduction in the rate of falls of 30% in one of the intervention groups relative to the control group during the inpatient period. This assumes a sample size of n = 390 per group, that the control group has a rate of falls of 15.7 per 1000 patient days, use of a Cox semi-parametric proportional hazards regression (Anderson-Gill extension for recurrent events) analysis approach and a two-tailed alpha of 0.05. Given that previous research in this setting similar to the present trial has been completed with no drop-outs, [17] we will recruit only an additional 3% of patients per group culminating in a sample size of n = 402 per group (n = 1206 in total). This sample size will also have 80% power to detect a one-third reduction in the proportion of patients who are fallers assuming that 24% of those in the control group will become fallers during their hospitalisation. The follow-up cohort of n = 117 per group will have 80% power to detect a 33% reduction in the proportion who are fallers assuming that 58% of the control group become fallers during the 6 month follow-up [46].

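### The primary falls model names no baseline covariate, although prognostic ones are collected; fixing them in advance would probably gain modest precision and settle an open covariate clause

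*Protocol article*

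**What the plan says.** Under Data Analysis, Primary Outcome, the protocol article analyses in-hospital falls by intention to treat with an Andersen-Gill extension of Cox regression, "with the intervention groups entered as dummy variables" and "using a two-tailed alpha = 0.05". It then says the approach allows repeated falls, differing lengths of stay and "time varying covariates to be incorporated into the analysis if required". It names no baseline covariate, site term or time-varying covariate, and no condition that would make one necessary. It does not call the model unadjusted.

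Under Outcome measures: "Demographic data being collected includes age, gender, falls in the 6 months prior to hospitalisation"; the same list goes on to cognitive status on a short mental-status questionnaire. The Procedure section puts baseline measurements after consent and before randomisation. The Discussion treats cognitive impairment as a consistent risk factor for hospital falls.

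Under Secondary Outcomes, adjustment for the EQ-5D analysis is fixed exactly (admission score and time between assessments). Length of stay gets open wording like that of the primary outcome, and post-discharge falls inherit the primary approach. The Randomisation section mentions no stratification.

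**The concern.** Fall risk varies greatly between patients, and the trial collects at least two variables likely to predict it. Placing them in the primary model in advance would remove part of the between-patient variation from the treatment comparison and deal with chance imbalance on them, with no added patients or data. As written, the article commits to none of them.

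The one covariate provision that does appear concerns variables that change during the stay. These are measured after allocation, so the education could affect some of them, and adjusting for those can bias the effect. With no list or trigger, the wording also leaves the final form of the primary model undecided. At stake are some precision and a clear statement of which model carries the primary conclusion.

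**Working it through.** **1. The stated power.** Inputs from the Sample size section: "80% power to detect a reduction in the rate of falls of 30% in one of the intervention groups relative to the control group"; "the control group has a rate of falls of 15.7 per 1000 patient days"; "This assumes a sample size of n = 390 per group".

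- Events needed (Schoenfeld): 4 × (1.960 + 0.842)² / (ln 0.70)² = 4 × 7.85 / 0.1272 = 247.
- Falls expected in two groups at mean stay L days: 390 × 0.0157 × (1 + 0.70) × L = 10.41 L. This reaches 247 at L = 23.7 days if falls are Poisson.

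The article gives neither mean stay nor between-patient dispersion, and its figure came from bootstrapping an earlier trial's data. The 80% can therefore be neither confirmed nor refuted, and it is the starting point below. The neighbouring figures reproduce: 24% versus 16% fallers gives 79.9% power at 390 per group and 81.1% at 402; 390 × 1.03 = 401.7; 117 per group follows with a continuity correction.

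**2. Variance reduction (simulation, all covariate inputs assumed).** There were 1500 trials per setting, with 390 per arm and rate ratio 0.70. Assumptions: 33-50% of patients on acute wards; 40% prior fallers with rate ratio 2.0-2.5; 30% cognitively impaired with rate ratio 1.8; residual frailty variance 0.8. A Poisson rate model with robust variance stood in for Andersen-Gill.

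- Variance of the log rate ratio, adjusted over unadjusted: 0.926, 0.913, 0.897 in three settings, a cut of 7-10%.
- Ward type alone gave 1-2%; prior falls and cognition gave most of the gain.
- Equivalent patients per arm: 390/0.926 − 390 = 31, to 390/0.897 − 390 = 45.
- Simulated power: 46.6% to 51.2%, 40.9% to 44.3%, 47.0% to 52.9%. The base is far below the stated 80%, so these gains do not carry over directly.

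**3. The same ratios applied at 80%.** Adjusted power = Φ(2.802/√ratio − 1.960).

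| Ratio | 2.802/√ratio | Power |
|---|---|---|
| 0.926 | 2.911 | 82.9% |
| 0.913 | 2.932 | 83.5% |
| 0.897 | 2.958 | 84.1% |

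**4. A wider range.** A negative binomial approximation, SE² = [(1/μ + k) + (1/(0.70μ) + k)]/390 with μ = 0.0157 L, was set so that unadjusted power is 80%. Covariates then explain a share of k.

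| Share of k explained | L = 25 days (k = 0.067) | L = 60 days (k = 1.872) |
|---|---|---|
| 10% | 80.1% | 82.3% |
| 20% | 80.2% | 84.7% |
| 30% | 80.2% | 87.1% |

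The gain is about 0 to 7 points. Holding power at 80% in this simple model implies 32-42% control fallers rather than the planned 24%, so it serves only to size the gain. A separate simulation with four assumed prognostic covariates moved power from 50% to 57% (mean stay 25 days) and from 57% to 65% (35 days), again from a lower base.

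**5. What an undecided model could allow.** In that last simulation with no true effect, taking the smallest p value from eight covariate sets raised type I error from 5.4% to 9.4% (25 days) and from 6.6% to 11.4% (35 days). One fixed adjusted model gave 5.9% and 6.8%, about the same as unadjusted. The sets were baseline covariates, so this is a worst-case illustration of free choice and includes no bias from post-randomisation variables.

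**The case against.** The strongest reply is that this is a condensed article. It never declares the model unadjusted, and a covariate list is commonly left to the full protocol or analysis plan. An unadjusted randomised comparison is valid, because its error rate already covers chance imbalance. The sentence on time-varying covariates can fairly be read as describing what an Andersen-Gill model can handle. All of this stands, so the open clause alone is mostly missing detail. What remains is that the article settles covariates where it chose to (EQ-5D) and commits the primary model only to group terms, so a concrete improvement can be named.

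A reader might infer that the primary model will be chosen on results, or adjusted for consequences of the education. The wording permits this but does not plan it. No time-varying covariate is named. Some, such as calendar period, could not be affected by the education, and a time-dependent term is also a usual response when proportional hazards fail, which the same section checks.

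A reader might also infer a nine-fold spread in fall rates across this trial's wards (20/2.2 = 9.1). The Background figures, "2.2 falls per 1000 patient days on general acute medical wards" and the upper value for rehabilitation wards, are published extremes from other studies. They do not describe the recruiting wards, and ward type added little in the simulation.

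Adjustment can change what a Cox hazard ratio means. This matters less here: a fall does not remove the patient from the risk set, so the rate ratio is largely unchanged by adjustment unless stay differs by arm and is related to risk.

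**Conclusion.** The point holds as a modest, no-patient-cost improvement. The primary model names only the group terms while likely prognostic baseline variables are at hand. The unadjusted analysis is valid but probably less precise than it could be. The best estimate is a rise from 80% to about 83-84% power, resting on assumed prevalences and rate ratios for prior falls and cognitive impairment and on a Poisson stand-in. Other assumptions give about 0 to 7 points, so the gain could be negligible.

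It also rests on reading prior falls and mental status as part of the pre-randomisation baseline. The article's list of demographic items does not say so item by item, and it includes discharge residence, which cannot be baseline. The documents do not support a claim that the planned analysis is invalid, that selection on results is intended, or that any stated power or sample size is wrong.

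**What to change.** Before outcomes are examined, state the primary model in full: Andersen-Gill with the two group terms, falls in the prior six months and baseline mental-status score as covariates, and site as a stratum or covariate. Add ward type at enrolment if it is recorded; the article's list of collected data does not mention it. Report the unadjusted estimate alongside. Replace the open clause with a statement that covariates measured after randomisation enter only labelled sensitivity analyses, and apply the same rule to the post-discharge falls analysis that inherits this approach.

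The cost is analysis wording only, with no extra patients and no new data beyond confirming ward type. With 1150 of 1206 participants already enrolled when the article was written, the wording should be settled promptly. If the sponsor prefers an unadjusted primary analysis, saying so explicitly would also close the open clause, at the price of the precision.
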